## METHODOLOGY

### DESIGN

To achieve the objectives of the study, a randomized controlled clinical trial will be designed to evaluate the clinical effects of the application of diacutaneous fibrolysis compared to the usual conservative treatment. Given its characteristics, it will be an analytical, longitudinal, prospective and experimental study.

### ETHICAL ASPECTS

This project will be presented to the Clinical Research Ethics Committee of Aragon (CEICA) and its approval is necessary to continue with the following stages of the study.

## STUDY VARIABLES

### INDEPENDENT VARIABLES

- Interventional treatment by diacutaneous fibrolysis on myofascial structures of the cranio-cervical region in the prone position.
- Control group, which will remain in the supine position for the same time as the intervention group with similar environmental conditions.

| VARIABLE                   | TYPE                    | TOOL      | VALUE                                                |
|----------------------------|-------------------------|-----------|------------------------------------------------------|
| Age                        | Discrete quantitative   | Anamnesis | Years                                                |
| Gender                     | Nominal qualitative     |           | Man / Woman                                          |
| BMI                        | Discrete quantitative   |           | Km/m                                     |
| Toxic habits               | Nominal qualitative     |           | alcohol / tobacco / drugs                            |
| Work activity              | Nominal qualitative     |           | Active / Unemployed / Retired                        |
| Position work activity     | Nominal qualitative     |           | Seated / Standing / Ambulation / Combined            |
| Hours of work activity     | Discrete quantitative   |           | Hours                                                |
| Physical activity          | Nominal qualitative     |           | Yes / No                                             |
| Hours of physical activity | Discrete quantitative   |           | Hours                                                |
| Analgesic medication       | Nominal qualitative     |           | Yes / No                                             |
| Headache history           | Continuous quantitative |           | Years                                                |
| headache frequency         | Discrete quantitative   |           | Days                                                 |
| Headache duration          | Discrete quantitative   |           | Minutes                                              |
| Location                   | Nominal qualitative     |           | Frontal / Occipital / Temporal / Parietal            |
| Quality of pain            | Nominal qualitative     |           | Oppressive / Throbbing / Continuous                  |
| Pain intensity             | Discrete quantitative   |           | VAS (100mm)                                          |
| Associated signs           | Nominal qualitative     |           | Vomiting / Phonophobia / Photophobia / Others / None |
| Need to lie down           | Nominal qualitative     |           | Yes / No                                             |
| Triggers                   | Nominal qualitative     |           | Yes / No                                             |
| Aggravating factors        | Nominal qualitative     |           | Yes / No                                             |

## DEPENDENT VARIABLES

| VARIABLE                            | TOOL                                                               |
|-------------------------------------|--------------------------------------------------------------------|
| Pain intensity                      | Visual analogue scale ( $r=0.94$ , $P < 0.001$ ) (44)              |
| Frecuency                           | Registration sheet                                                 |
| Duration                            | Registration sheet                                                 |
| Localization                        | Registration sheet (topographic map)                               |
| Pressure pain threshold             | Pressure algometer $r=0,92$ (ICC) (45)                             |
| Muscle tenderness                   | Manual assessment (criteria according to Langemark and Olesen)(18) |
| Mobility of the intermuscular septa | Manual asesment                                                    |
| Muscle length                       | Manual asesment                                                    |
| Deep flexor muscle strength         | Cranio-cervical flexion test $r=0.63-0.86$ (ICC) (46)              |
| Cervical Range of Motion            | CROM $r=0.87-0.94$ (ICC) (46)                                      |
| Forward head position               | Photographic camera interexaminer $r>0.85$ (47)                    |
| Cross section of cervical muscles   | Ultrasound                                                         |
| Disability                          | HIT-6 Questionnaire                                                |
| Quality of life                     | COOP-WONCA Questionnaire                                           |

The variables have been chosen based on a review carried out in 2013 by J. Abboud in which he selected the most used musculoskeletal variables in the evaluation of patients with tension-type headache in clinical trials. (20). In addition, variables have been added that assess muscle parameters that may be relevant, as well as quality of life and disability to see the impact of this pathology on the daily life of these patients.

## STUDY SAMPLE

### SAMPLE SIZE

The variable improvement in headache frequency has been chosen as a reference for calculating the sample size.

The calculation was made with the online program GRANMO 7.12 with the comparison menu between two independent means with a unilateral contrast and the following values: alpha risk 0.05; beta risk 0.20; to detect a difference equal to or greater than 3 units; a common standard deviation of 5 units; a ratio between the number of subjects between groups 1 and estimating a 15% loss to follow-up. The result is that 41 subjects per group are needed, as in this study there will be two groups, there are 82 subjects in total. Recruitment of this number of subjects is expected to be feasible.

The statistical data necessary to perform the calculation have been obtained from the study by Castien et al.(48) on the comparison of the application of manual therapy techniques versus usual medical treatment in patients with chronic tension-type headache, with an outpatient population in the Netherlands area.

#### Recruitment and obtaining the sample

Participation in the study will be offered to patients from different primary care services in the Zaragoza metropolitan area. Those patients who, being diagnosed with tension-type headache by the doctor responsible for each service, may be likely to benefit from participation in this study will be informed of the study.

#### INCLUSION AND EXCLUSION CRITERIA

##### *Inclusion criteria:*

- Present a diagnosis of episodic or chronic tension-type headache, made by a medical professional in the area of neurology, following the fundamental diagnostic criteria for tension-type headache established in the International Classification of Headaches (ICHD-III).
- Be over 18 years of age.
- Ability to fill in the questionnaires.
- Attendance at all intervention and assessment sessions.
- Reading of the informative document and signing of the informed consent.

##### *Exclusion criteria:*

- Involvement in compensation or litigation for health problems.
- Receive physiotherapy treatment in the cranial-cervical region in the month prior to the study or during it. However, the subject is allowed to continue on palliative medication that continues until the completion of the study for ethical reasons and to facilitate the accuracy of the study.
- Subjects with the presence of red flags for headaches(49), as well as subjects who may have severe diseases that may be related to clinical outcomes: malignancy or history of cancer, vertebral infection, tumors or vertebral fractures, lumbar instability, blood dyscrasia, severe trauma in the previous 3 months, neck surgery in the previous 12 months, referred neck pain of visceral origin.
- Insufficient understanding of Spanish.
- Change of usual medication guidelines in the last month.
- Not completing all the proposed sessions.

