## DESCRIPTION OF THE INTERVENTION

Once the sample has been selected, an initial evaluation will be carried out, collecting data on the patient's clinical history using the anamnesis variables mentioned above. In addition, to identify more clinical characteristics of the sample of patients with tension-type headache, together with the clinical history, an assessment will be made of: the pressure pain threshold in the most relevant muscles of the cervical region by assessment with an algometer of pressure, cervical range of motion in the three planes of space using the CROM cervical range of motion measuring device and muscle length of the cervico-scapular muscles, the forward head position in sitting and standing by photometry, the resistance of the flexor musculature by means of the craniocervical flexion test (50) and the cross-sectional area of the deep cervical musculature by ultrasound.

Both groups will attend 3 sessions on alternate days for a week. Each of the sessions will consist of a pre-intervention assessment (intensity, frequency and location of the pain), an intervention (DF in the cranio-cervical region / Control) and a post-intervention assessment (intensity, frequency and location of the pain). In addition, a final complete assessment will be carried out 4 weeks after the last intervention. This assessment will be carried out throughout the study in the same time slot and will be preceded by some active warm-up exercises by the patient. The approximate time of each session will be 60 minutes.

Each treatment session of the Intervention Group will consist of a DF session in the cranio-cervical region, for 30 minutes, which will be directed mainly to the approach to the edges, insertions and insertional tendinous tissue of the following muscles: trapezius, paravertebral, angular scapulae, splenius capitis and neck, suboccipital, sternocleidomastoid, and temporal. The patient will be informed that the technique must be painless at all times and only a slight pricking sensation is allowed during hook traction (below 3 out of 10 on a VAS scale). The Control Group will receive the same assessments and will remain in the supine position for the same treatment time without receiving any intervention.

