#### DATA COLLECTION AND ANALYSIS

Those patients of the previously mentioned medical services, likely to participate in this study according to the corresponding medical specialist and who meet the inclusion and exclusion criteria will be referred to a physiotherapist to provide them with the information (oral and written) of the study. Those patients who decide to collaborate must sign the informed consent and will be assigned a correlative number. This same physiotherapist will be in charge of carrying out the initial, post-intervention and follow-up assessment, remaining blind to the assigned group. This assessment will include: Anamnesis, distribution of questionnaires, collection of data on the examination sheet related to pain, examination of the joint and muscular function of the cervical region, taking photographs to analyze posture and performing several ultrasounds of the cervical musculature.

A second physiotherapist, who will be the only one with access to the randomization list, will apply the diacutaneous fibrolysis technique to the patients assigned to the intervention group. It will also record the possible incidents or complications that may have occurred, such as bruises, skin reactions, etc.

As it is a manual technique, the physiotherapist cannot be blinded to the patient's condition, but allocation concealment is respected with this procedure.

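### Three eligibility conditions can be judged only after randomisation and, read literally, remove randomised patients whose outcome could have been obtained

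*Protocol*

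**What the plan says.** Three items in the Protocol's eligibility lists concern events during the trial:

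- Inclusion criteria: "Attendance at all intervention and assessment sessions".
- Exclusion criteria: "Not completing all the proposed sessions".
- Exclusion criteria: "Receive physiotherapy treatment in the cranial-cervical region in the month prior to the study or during it". The first half of this item is an ordinary baseline criterion; the last three words are not.

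The schedule is under Description of the intervention: "Both groups will attend 3 sessions on alternate days for a week", and then "a final complete assessment will be carried out 4 weeks after the last intervention". The control group "will remain in the supine position for the same treatment time without receiving any intervention".

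Two other places bear on the point. Data collection and analysis says that patients "who meet the inclusion and exclusion criteria will be referred to a physiotherapist", who then informs them, obtains consent and gives them a number. Sample size arrives at 41 per group while "estimating a 15% loss to follow-up".

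**The concern.** The treatment sessions differ by allocated group, and the last assessment comes four weeks after them. Whether a patient attended everything, finished every session or sought other physiotherapy is therefore settled only after allocation. A criterion that rests on those facts cannot screen anyone at entry. It can act only on someone already randomised.

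If the criteria are applied as written, a patient who misses a session or has physiotherapy elsewhere becomes ineligible even when the 4-week outcome is available. The remaining groups are then selected by what happened under treatment. Patients can see whether they receive hook treatment or lie untreated, so the reasons for dropping out or seeking other care may differ between the arms. If removal is also related to outcome, the estimated difference is biased. The 15% allowance replaces numbers but does not correct selection.

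**Working it through.** **1. The passages side by side**

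| Place in the Protocol | What it implies |
|---|---|
| Inclusion and exclusion criteria | Attendance, completion and absence of physiotherapy during the study decide eligibility |
| Data collection and analysis | Eligibility is settled before referral, consent and numbering |
| Sample size | 15% of participants will be lost to follow-up |

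No patient can satisfy the first row at the time fixed by the second. Under the first row a patient lost to follow-up was never eligible, yet the third row budgets for such patients as members of the trial.

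**2. The plan's own figure**

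Inputs from Sample size: difference 3, SD 5, one-sided alpha 0.05, power 0.80, ratio 1, loss 15%.

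n = 2 × [5 × (1.645 + 0.842) / 3]² = 34.35 per arm. Dividing by 0.85 gives 40.4, so 41 per arm and 82 in total. The stated figure reproduces. The loss allowed for is 0.15 × 41 ≈ 6 per arm, or about 12 overall.

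**3. How large the bias could be**

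The documents do not say how many patients these criteria would remove or how removal relates to outcome. The following is an illustration under assumptions:

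- 41 per arm, improvement normally distributed with SD 5, no true effect.
- Completion score = ρ × (improvement / 5) + √(1 − ρ²) × independent standard normal noise.
- In the selective arm the k patients with the lowest score are removed; in the other arm k are removed at random.
- One-sided t-test at 5%, matching the one-sided contrast in Sample size.

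| Selective removal | k per arm | ρ | Bias in favour of fibrolysis (units) | One-sided error |
|---|---|---|---|---|
| Fibrolysis arm only | 1 to 2 | 0.3 to 0.5 | about 0.1 to 0.3 | about 6% to 8% |
| Fibrolysis arm only | 6 | 0.3 to 0.5 | about 0.4 to 0.7 | about 10% to 14% |
| Fibrolysis arm only | 6 | 1 (extreme) | about 1.3 | about 33% |
| Control arm only | 6 | 0.3 to 0.5 | about −0.4 to −0.7 | about 2.6% down to 1.5% |
| Both arms equally | 6 | 0.3 to 0.5 | about 0 | about 5% |

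A closed-form check of the extreme case: removing the worst 15% of a normal distribution shifts the mean by SD × φ(z₀.₈₅) / 0.85 = 5 × 0.233 / 0.85 = 1.37 units, which is 1.37 / 3 = 46% of the target difference. The simulated 1.3 is slightly smaller because 41 is a finite sample and 6 / 41 is just under 15%.

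**4. Power if everyone is kept**

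With the plan's inputs and a one-sided test, power is 80.7% with 35 per arm observed and 85.8% with all 41 observed.

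**The case against.** The strongest reply is that nothing in the Protocol says who is analysed. The analysis section names no analysis set, and that is commonly left to a statistical analysis plan, which is not at hand. The attendance item could also be read as a commitment given at entry. Part of this stands: the silence on analysis sets is not a finding, and a reader might infer that the trial has become a completers-only comparison, which the document never states. The eligibility wording is a different matter. The non-completion item cannot easily be read as a promise, and an analysis plan that kept everyone would contradict these criteria.

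The second reply concerns size, and it stands. The 15% is loss to follow-up. Those patients would mostly have no 4-week outcome under any wording. Only patients whose outcome was obtainable but discarded count against these criteria, and their number is not given. Exposure is also short: three sessions in a week and one later visit. Six per arm is therefore an upper illustration.

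Third, a reader might infer that the false-positive rate must rise. The documents do not support that. If untreated controls leave because they are not improving, the control mean is flattered and the one-sided error falls below 5%. It is also only possible, not established, that reasons for leaving differ by arm: the technique is meant to be painless, bruising is listed only as a possible incident, and the assessor and the analyst are blinded. That blinding does not, however, prevent selection by attendance.

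**Conclusion.** The point holds as a defect in what the Protocol states. Two whole criteria and half of a third depend on events after randomisation. They conflict with the timing of eligibility under Data collection and analysis and with the planned 15% loss under Sample size, and nothing elsewhere in the document offsets them. Read literally, they allow randomised patients with obtainable outcomes to be removed, and the protection of randomisation is weakened to that extent.

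The consequence is a possible bias of unknown direction. If one or two patients per arm are discarded it is small, at most about a tenth of the 3-unit target at the correlations assumed. At six per arm it could reach roughly 0.4 to 0.7 units, or 13% to 23% of the target (0.4 / 3 and 0.7 / 3). These sizes rest on assumed correlations and on selective removal in one arm only. They are not predictions for this trial.

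**What to change.** - Replace the attendance item with: *willing and able at enrolment to attend all sessions*.
- Delete non-completion of sessions as an exclusion criterion.
- Keep the month before the study as the baseline physiotherapy criterion. Move the words about physiotherapy during the study out of eligibility and into the study-conduct instructions. The restriction itself stays, because the existing request not to change treatment does not name physiotherapy. Breaches are recorded as protocol deviations and are not grounds for removal.
- State that all randomised patients are analysed in their assigned group.
- Seek the planned 4-week outcomes from every reachable patient, whether or not sessions were missed or other physiotherapy was received. The algometer, range-of-motion and ultrasound measures need a visit and cannot be recovered by questionnaire.
- Keep the completers' comparison as a sensitivity analysis.

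The cost is the rewording of three items, one sentence on analysis and some follow-up effort. Non-adherence may slightly dilute the estimated effect. The sample size stays at 82.

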## RANDOMIZATION

The subjects will be randomly assigned to an Intervention Group by means of FD in the cranio-cervical region (Group A) or to a Control Group (Group B). The randomization process will be carried out through a systematic random sampling, together with the creation of a list of random numbers (1 and 2) created from a computer application for randomization of numbers (1 = Group A; 2 = Group B).

## DESCRIPTION OF THE INTERVENTION

Once the sample has been selected, an initial evaluation will be carried out, collecting data on the patient's clinical history using the anamnesis variables mentioned above. In addition, to identify more clinical characteristics of the sample of patients with tension-type headache, together with the clinical history, an assessment will be made of: the pressure pain threshold in the most relevant muscles of the cervical region by assessment with an algometer of pressure, cervical range of motion in the three planes of space using the CROM cervical range of motion measuring device and muscle length of the cervico-scapular muscles, the forward head position in sitting and standing by photometry, the resistance of the flexor musculature by means of the craniocervical flexion test (50) and the cross-sectional area of the deep cervical musculature by ultrasound.

Both groups will attend 3 sessions on alternate days for a week. Each of the sessions will consist of a pre-intervention assessment (intensity, frequency and location of the pain), an intervention (DF in the cranio-cervical region / Control) and a post-intervention assessment (intensity, frequency and location of the pain). In addition, a final complete assessment will be carried out 4 weeks after the last intervention. This assessment will be carried out throughout the study in the same time slot and will be preceded by some active warm-up exercises by the patient. The approximate time of each session will be 60 minutes.

Each treatment session of the Intervention Group will consist of a DF session in the cranio-cervical region, for 30 minutes, which will be directed mainly to the approach to the edges, insertions and insertional tendinous tissue of the following muscles: trapezius, paravertebral, angular scapulae, splenius capitis and neck, suboccipital, sternocleidomastoid, and temporal. The patient will be informed that the technique must be painless at all times and only a slight pricking sensation is allowed during hook traction (below 3 out of 10 on a VAS scale). The Control Group will receive the same assessments and will remain in the supine position for the same treatment time without receiving any intervention.

Participants in both groups will be asked not to modify treatment guidelines or regular physical exercise, or hours of sleep and, to the extent possible, not to vary very markedly the activities of their daily life during the period. how long the study lasts.

#### DATA COLLECTION AND ANALYSIS

Those patients of the previously mentioned medical services, likely to participate in this study according to the corresponding medical specialist and who meet the inclusion and exclusion criteria will be referred to a physiotherapist to provide them with the information (oral and written) of the study. Those patients who decide to collaborate must sign the informed consent and will be assigned a correlative number. This same physiotherapist will be in charge of carrying out the initial, post-intervention and follow-up assessment, remaining blind to the assigned group. This assessment will include: Anamnesis, distribution of questionnaires, collection of data on the examination sheet related to pain, examination of the joint and muscular function of the cervical region, taking photographs to analyze posture and performing several ultrasounds of the cervical musculature.

A second physiotherapist, who will be the only one with access to the randomization list, will apply the diacutaneous fibrolysis technique to the patients assigned to the intervention group. It will also record the possible incidents or complications that may have occurred, such as bruises, skin reactions, etc.

As it is a manual technique, the physiotherapist cannot be blinded to the patient's condition, but allocation concealment is respected with this procedure.

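### The assessor declared blind appears to take the pain record right after each session, so blinding of the examiner-dependent 4-week outcomes is at avoidable risk

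*Protocol*

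**What the plan says.** Data Collection and Analysis in the Protocol assigns all assessments to one physiotherapist: "This same physiotherapist will be in charge of carrying out the initial, post-intervention and follow-up assessment, remaining blind to the assigned group". A second physiotherapist gives the treatment, is the only holder of the randomization list, and records "possible incidents or complications that may have occurred, such as bruises, skin reactions, etc". The section concludes that this arrangement preserves allocation concealment.

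The Description of the Intervention sets the timetable: "Both groups will attend 3 sessions on alternate days for a week". Each session has a pain assessment before the intervention, the intervention, and then "a post-intervention assessment (intensity, frequency and location of the pain"). On length: "The approximate time of each session will be 60 minutes". The treated group receives "a DF session in the cranio-cervical region, for 30 minutes". The control group "will remain in the supine position for the same treatment time without receiving any intervention". A complete assessment follows 4 weeks after the last session.

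The Dependent Variables table lists 14 outcomes. They include muscle tenderness, mobility of the intermuscular septa and muscle length, all three assessed manually.

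**The concern.** The Protocol states assessor blinding as a fact, but its own visit structure seems to put the assessor in front of each patient when the allocation is easiest to discover. The patient has just had half an hour of hook traction on the neck and head, or half an hour of lying still, knows which it was, and is then asked about pain. Marks on the skin, where they occur, would be freshest then.

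What is learned in the session week stays with the assessor. The same person performs the 4-week examination, where several outcomes depend on how the examiner presses, moves or scores. Because patients cannot be blinded in this design, a blind assessor is the main protection those outcomes have. If that blinding is lost, detection bias can enter them, and a published statement that the assessor was blind would claim more than the procedure secures.

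**Working it through.** The point is procedural. It is checked by setting the sections side by side, with simple counts.

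**1. Who meets the patient after treatment.** The Description of the Intervention does not name the person who takes the session pain record. Data Collection and Analysis gives the post-intervention assessment to the blinded physiotherapist. The shared term links the two, so the assessor appears to take the record. This is an inference, though the natural one.

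**2. How soon.** A session lasts about 60 minutes, of which 30 are treatment: 60 − 30 = 30 minutes for everything else. The post-session contact therefore falls in the same visit, at most about half an hour after treatment ends.

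**3. How often.** There are three post-session contacts per patient. Pre-session contacts at sessions 2 and 3 also come after the first treatment, so 3 + 2 = 5 contacts precede the 4-week visit. With the planned 41 per group, the treated arm has 41 × 3 = 123 post-treatment contacts.

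**4. Routes to unblinding.**
- Speech: there is no sham, so patients in both arms know what they received.
- Skin: marks such as bruises are named as possible, and the treated sites include the trapezius, sternocleidomastoid and temporal muscles, which lie in visible areas.

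**5. Stated safeguards.** The only one in the text at hand is that the treating physiotherapist alone holds the list. That keeps the assessor from reading the allocation, but not from seeing or hearing it. Allocation concealment concerns what is known before assignment. It does not keep an assessor blind afterwards.

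**6. Which outcomes are exposed.** Sorting the 14 dependent variables:
- Examiner-administered (8): pressure pain threshold, muscle tenderness, septal mobility, muscle length, cranio-cervical flexion test, cervical range of motion, forward head position by photograph, muscle cross-section by ultrasound. Tenderness, septal mobility and muscle length are purely manual.
- Self-reported (6): pain intensity, frequency, duration, location, HIT-6, COOP-WONCA.

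**7. Bearing on the sample size.** None. The stated figure reproduces: 2 × [5 × (1.645 + 0.842) / 3]² = 34.35 per group, and 34.35 / 0.85 = 40.4, rounded up to 41. It rests on headache frequency, which comes from a registration sheet.

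**The case against.** - **The session contact is uncertain and limited.** Data Collection and Analysis goes on to list a full battery (history, cervical examination, photographs, ultrasound), so its post-intervention assessment could be one fuller assessment after the course and not the three session records. This stands as a limit on certainty, hence the word appears. A reader might infer that the assessor physically examines each patient after every session. The Description of the Intervention supports only a record of pain intensity, frequency and location. A pain record is still a face-to-face conversation with a patient who knows the arm.

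- **Marks may be rare.** The Protocol describes the technique as painless and as preserving the integrity of the skin, and it calls bruises possible incidents. It would be wrong to read it as expecting them. This weakens the skin route but leaves the speech route untouched.

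- **A safeguard may exist elsewhere.** Consent pages are not available here, and an instruction not to disclose treatment could sit there. The point is therefore confined to what the available text describes.

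- **A number is tempting.** Suppose the arm is revealed in 10%, 20% or 40% of sessions, independently. Then 1 − (1 − m)³ gives 27%, 49% and 78% of treated patients unblinded before week 4. Nothing in the documents supports those per-session risks, and independence is doubtful because talkativeness and a tendency to bruise belong to the patient. With full within-patient correlation the figures stay at 10%, 20% and 40%. These values should not be quoted as an estimate.

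- **The main outcome is hardly touched.** This stands. Bias in self-reports comes mainly from patients knowing their arm, which is a different matter.

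**Conclusion.** The point holds in a limited form. The Protocol asserts assessor blinding while its schedule appears to bring the assessor together with unblinded patients three times directly after treatment, and the one stated safeguard closes neither the speech route nor the skin route. At risk are the 8 examiner-administered variables at 4 weeks, most of all the 3 purely manual ones. The probability of unblinding, and the bias that would follow, cannot be derived from the documents.

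The conclusion assumes that the post-intervention assessment assigned to the blinded physiotherapist includes the session pain records, and that no non-disclosure instruction exists in material not available here. A reader might go further and infer that blinding will fail, or that the headache-frequency result is compromised by this route. The documents support neither. This is an avoidable weakness that should be corrected. It does not undermine the trial's main comparison.

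**What to change.** Amend the Description of the Intervention and Data Collection and Analysis together:

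1. Patients complete the pre- and post-session items (pain intensity, frequency, location) themselves and alone, and deposit the sheet in a sealed envelope or closed box with neither physiotherapist present. Handing it to the treating physiotherapist should be avoided, because ratings given in that person's presence invite response bias.
2. The blinded assessor sees patients only at baseline and at 4 weeks.
3. Patients are told, at consent and again before the 4-week visit, not to reveal what they received. With no sham, this instruction is the only one of these measures that acts against disclosure at the 4-week visit itself.
4. The assessor's guess of allocation is recorded at 4 weeks, so that the blinding claim can be examined.
5. The text states who takes the session record and what the post-intervention assessment contains. If a full hands-on battery after the course is intended, it stays with the assessor under the same non-disclosure instruction.

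The cost is revised wording, forms, and envelopes or a box. No extra staff are needed, and no treatment or outcome changes. The items are self-reports, and the inclusion criteria already require patients to be able to complete questionnaires. The downside is that session scores are self-completed and not checked on the spot, so some entries may be missing or unclear.
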